## Abstract

**Background**: A sedentary behavior and being overweight represent major public health issues associated with both physical and psychological risks. Based on self-determination theory (SDT), the psychoeducational intervention PsicoFIT—a component of the TIGREFIT program—aims to foster motivation toward physical activity, to promote healthy habits, and to reduce psychological ill-being in sedentary adults who are overweight and are fans of a football club. **Methods**: This protocol corresponds to a longitudinal comparative pragmatic clinical trial, designed in accordance with the recommendations of the SPIRIT Statement. The intervention, preceded by a training program for the coaches involved, will comprise 12 weekly modules delivered in two modalities: (1) face-to-face, through group sessions, and (2) semi face-to-face, through short video capsules hosted on a digital platform. Changes associated with the intervention will be evaluated using hierarchical multiple regression and pre-post comparisons, assessing baseline and post-intervention data within and between the intervention modalities. Primary outcomes will include changes in healthy lifestyle and burnout as indicators of well-being and ill-being, respectively. Secondary outcomes will assess basic psychological needs satisfaction and autonomous motivation as potential mediators of these effects, as well as the coach’s controlling interpersonal style as a possible contextual predictor. The modality of participation will be analyzed as a potential moderator of the observed changes. Finally, the acceptability and perceived contribution of the intervention will be explored through a focus group. **Discussion**: PsicoFIT will provide a methodological framework for designing interventions within multicomponent programs aimed at promoting healthy lifestyles and psychological well-being in sedentary adults who are overweight, considering the social context of football fandom and allowing for an exploration of the impact of the face-to-face and semi-face-to-face modalities. Future empirical application of the protocol will help verify its effectiveness, guide adaptations across contexts, and contribute to the development of evidence-based interventions. **Conclusions**: The implementation of PsicoFit will allow for the evaluation of its effectiveness, psychological mechanisms, and delivery modalities, thus guiding future evidence-based interventions in sport.

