**Hypothesis** **2.**
*Significant changes in the coach’s controlling interpersonal style, basic psychological need satisfaction, autonomous motivation, healthy lifestyle, and burnout are expected at post-intervention compared to baseline. Additionally, the magnitude of these changes may differ between the face-to-face and semi face-to-face modalities.*

Specific Objective 3a. To evaluate the mediating effect of the satisfaction of basic psychological needs and autonomous motivation between the coach’s controlling interpersonal style and healthy lifestyle (mediating effect 1), as well as between the coach’s controlling interpersonal style and burnout (mediating effect 2) in both the face-to-face and semi face-to-face modalities, at baseline and post-intervention.

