#### 2.2.4. Sample Size and Randomization

The study will employ a non-probabilistic convenience sampling [44], including participants who meet the established inclusion criteria and are available during the recruitment period.

The sample size (*n* = 80) was determined pragmatically and based on operational feasibility, considering the resources and organizational requirements of the intervention, including the facilitators’ capacity, the availability of staff responsible for implementation, the total program duration, and the estimated recruitment period.

The participants will be distributed equally between the two intervention modalities, with 40 participants per modality (20 men and 20 women in each; see Table 1).

Randomization will be conducted using a computer-generated procedure, applying stratification to ensure an equitable distribution between the groups. The randomization will be generated and safeguarded by a researcher independent of the intervention. Once the assignment is generated, each participant will be notified individually.

Blinding of the participants and facilitators is not feasible due to the nature of the intervention delivery format. The face-to-face and semi face-to-face modalities differ in observable aspects, such as the type of interaction, communication channels, and module dynamics, making it impossible to conceal the assigned modality. Nevertheless, participants will not receive information regarding the activities or specific structure of the alternative modality. Likewise, facilitators will necessarily be aware of the format of the modality they deliver.

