### 2.6. Data Analysis

#### 2.6.1. Quantitative Analysis

Due to the practical limitations in following up with those participants who do not complete the program, the primary analysis will be conducted using a per-protocol approach [111], considering only those participants with complete data at baseline and at the end of the intervention; missing data will not be imputed.

This approach will allow for evaluating the changes associated with each intervention under real-world implementation conditions, acknowledging the anticipated risk of participant attrition and that the benefits of randomization may not be fully preserved, while reflecting its applicability in a pragmatic context.

All statistical analyses will consider a 95% confidence level (5% error), ensuring transparency and reproducibility.

Preliminary Analysis. Descriptive statistics for central tendency (mean, median), dispersion (standard deviation and variance), and distribution (skewness and kurtosis) will be estimated for each observed variable. Next, normality tests will be conducted, and the reliability of the instruments will be estimated by measuring their internal consistency through Cronbach’s alpha (α) and McDonald’s omega (ω) coefficients. Subsequently, bivariate correlation analyses will be performed to measure the strength and direction of the relationship between the variables.

Associations among motivational and outcome variables. To examine the associations between the coach’s controlling interpersonal style, basic psychological need satisfaction, autonomous motivation, healthy lifestyle, and burnout, hierarchical multiple regression analyses will be conducted. Separate models will be estimated for each intervention modality (face-to-face and semi face-to-face) and for each measurement occasion (baseline and post-intervention), with predictor variables entered in a theoretically driven manner [42]. Effect sizes and confidence intervals will be calculated to complement the statistical significance, and statistical power will be considered when interpreting the results [112].

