Intervention-related changes. Changes in the coach’s controlling interpersonal style, basic psychological need satisfaction, autonomous motivation, healthy lifestyle, and burnout from baseline to post-intervention will be examined. Within-group pre-post comparisons will be conducted for each intervention modality (face-to-face and semi-face-to-face). Between-group comparisons will assess whether the magnitude of changes differs between the two modalities [42]. Effect sizes will be calculated to quantify the magnitude of the observed changes, and statistical power will be considered in interpreting the results [113].

Mediation effects. The effects of basic psychological needs satisfaction and autonomous motivation as mediating variables (the mediation effect of basic psychological needs satisfaction and autonomous motivation on the relationship between the coach’s controlling interpersonal style, healthy lifestyle, and burnout, as well as the effect of basic psychological needs satisfaction on the relationship between autonomous motivation, healthy lifestyle, and burnout) will be evaluated using regression-based mediation analyses with bootstrapping procedures to estimate direct and indirect effects following Hayes’s recommendations [43], considering pre- and post-intervention data. The significance of mediation inferred when the confidence interval of the indirect effect does not include zero allows for the assessment of whether the observed relationships are explained directly or indirectly through the proposed mediating variables. Mediation effects will be considered exploratory due to the sample size and the nature of the study.

Moderation Effects. The moderating effects of both intervention modalities will be evaluated using regression-based moderation analyses, following Hayes’s recommendations [43], considering both pre- and post-intervention data. Moderation will be examined by including interaction effects, as evaluated through bootstrapped confidence intervals. Significant interaction effects will indicate that the strength or direction of the relationship between predictors and outcomes differs according to the intervention modality. Moderation effects will be considered exploratory due to the sample size and the nature of the study.

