#### 2.7.1. Primary Outcomes

Healthy lifestyle (well-being): Behaviors related to nutrition, physical activity, and other healthy habits will be assessed as indicators of well-being.Burnout (ill-being): Physical and emotional exhaustion, sense of accomplishment, and devaluation of sports practice will be evaluated as indicators of ill-being.The variable of interest in both cases will be the change after the intervention, calculated as the difference between post-intervention and baseline scores.

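### Two unranked primary outcomes are each compared between modalities at 5% with no decision rule, so if either alone can support a claim, the chance of a false primary difference is up to about 10%

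*Protocol article*

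**What the plan says.** All places are in the protocol article.

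- **Primary outcomes.** The abstract says: "Primary outcomes will include changes in healthy lifestyle and burnout as indicators of well-being and ill-being, respectively". Section 2.7.1 lists the same two and fixes the metric: "The variable of interest in both cases will be the change after the intervention, calculated as the difference between post-intervention and baseline scores". Neither outcome is put first.
- **Comparison.** Under intervention-related changes, 2.6.1 plans pre-post tests within each modality and then a contrast of the modalities: "Between-group comparisons will assess whether the magnitude of changes differs between the two modalities". This covers all five study variables, the two primaries among them.
- **Hypothesis.** Hypothesis 2 states the modality part without a direction: "Additionally, the magnitude of these changes may differ between the face-to-face and semi face-to-face modalities". It does not say whether one outcome or both must differ.
- **Error level.** Section 2.6.1: "All statistical analyses will consider a 95% confidence level (5% error), ensuring transparency and reproducibility".
- **What is called exploratory.** Section 2.6.1 labels the mediation analyses exploratory and says of moderation: "Moderation effects will be considered exploratory due to the sample size and the nature of the study". The change comparisons carry no such label.
- **Size.** Section 2.2.4 allocates 80 participants equally, "with 40 participants per modality". The number rests on feasibility, and no effect size, SD or power is given.

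**The concern.** The modality contrast is the only randomised comparison in the trial, and two outcomes of equal standing are tested for it. Each test gets the full 5%. With no ranking, joint requirement or adjustment, a significant result on either outcome could be presented as a primary difference between modalities, and the article does not say how to read one significant and one non-significant result.

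Two things are at stake. The first is the error rate of the primary modality claim taken as a whole, which is higher than the level of each test. The second is interpretation: in a feasibility-sized trial a split result is quite possible, and a rule chosen after the data are seen will not be convincing.

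**Working it through.** **Inputs**

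- Level per analysis: 0.05 (2.6.1).
- Primary between-modality tests: 2, one per primary outcome (2.7.1 and 2.6.1).
- Sidedness: not stated. Taken as two-sided because Hypothesis 2 is non-directional (assumption).
- Arm size: 40 (2.2.4).
- Correlation between the two change scores: not given. A range of 0 to 0.9 in absolute size is used (assumption). Hypothesis 1 links autonomous motivation positively to lifestyle and negatively to burnout, so a negative sign is plausible, but the sign does not matter for two-sided tests.

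**Step 1. The plan's own figure.** A two-sided test at z = 1.96 has an error of 0.0500, which matches the stated 95% confidence and 5% error. The article has no power calculation to reproduce.

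**Step 2. Two tests, both null hypotheses true.**

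- Independent outcomes: 1 − (1 − 0.05)² = 1 − 0.9025 = 0.0975.
- Upper bound under any dependence: 0.05 + 0.05 = 0.10.
- Correlated outcomes: 1 − P(|Z1| < c and |Z2| < c), with (Z1, Z2) standard bivariate normal with correlation r. Here c = 1.96 for 5% per test and c = 2.24 for 2.5% per test.

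| Absolute r | At least one false result, 5% each | Same, 2.5% each (also Holm when both nulls are true) |
|---|---|---|
| 0 | 9.75% | 4.94% |
| 0.3 | 9.51% | 4.84% |
| 0.5 | 9.07% | 4.65% |
| 0.7 | 8.35% | 4.30% |
| 0.8 | 7.81% | 4.02% |
| 0.9 | 7.04% | 3.62% |

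Simulated t-tests with 40 per arm (100,000 replicates) agree: 9.77% at r = 0, 9.68% at −0.3, 9.14% at −0.5 and 8.31% at −0.7. Apart from small-sample detail, the result does not depend on the sample size.

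**Step 3. Cost in detectable difference.** With n = 40 complete cases per arm and 80% power, the normal approximation is d = (z for 1 − α/2 + z for 0.80) × √(2/n), where √(2/40) = 0.2236.

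- α = 0.05: (1.960 + 0.842) × 0.2236 = 0.63. The t-based value is 0.634.
- α = 0.025: (2.241 + 0.842) × 0.2236 = 0.69. The t-based value is 0.701.

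The t-based values are the ones used below, in SD units of the change score.

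**The case against.** **It can be left to the analysis plan.** Multiplicity rules often are, and a condensed article need not carry them. Silence alone would be no finding. But the article is not silent about the level: it fixes 5% for all analyses, names two primaries of equal rank, and reserves the exploratory label for mediation and moderation. A later rule would at least have to qualify that sentence. Reading the 5% as a general convention that a Holm rule could sit beside is possible, and that is a reason for a clarification rather than a graver charge.

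**The 5% is per analysis.** This stands. A reader might infer that the stated 5% is wrong, or that a promised overall error is not delivered. The article never claims control across outcomes, so its figure is neither miscalculated nor broken.

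**Well-being and ill-being are separate questions.** If each outcome supports only its own claim, joint control is a matter of preference. The article does not say so, nor does it say that either outcome suffices. The size given here is therefore conditional on that use.

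**Factor-level testing.** Section 2.7.1 describes the primaries by their components, and only 2.7.2 fixes total scores, so a reader might infer that the ten lifestyle and three burnout factors will each be tested between modalities. No section plans this. Section 2.7.1 speaks of one variable of interest per outcome, and the hypotheses treat each outcome as a single variable. Nor do the within-modality pre-post tests belong in the count, since they are not randomised comparisons.

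**The inference is already limited.** The article concedes that the completers-only analysis may not fully preserve randomisation, and it plans effect sizes with power weighed in interpretation. That is fair: an alpha rule does not repair attrition bias. It does not remove the need for one.

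**Conclusion.** The point holds in a conditional form. The 5% level is correct for each analysis, but it is applied to two unranked primary outcomes with no rule for combining them. If either outcome alone can support a claim of a modality difference, the chance of at least one false primary difference is up to about 10%.

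The 9.75% is the independence value and close to the maximum; at correlations of 0.5 and 0.7 it is about 9% and 8%. These figures assume two-sided tests and no true difference on either outcome. The weakness bears on how the main randomised result will be read. It does not invalidate the trial.

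**What to change.** Add to 2.6.1, and mirror in 2.7.1, wording such as:

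*The confirmatory family is the between-modality difference in change in the two primary outcomes, each analysed as one total score and tested with the Holm procedure at an overall two-sided 5%. Within-modality tests, factor scores and secondary outcomes are supportive and are reported with confidence intervals.*

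This holds the chance of any false primary difference to at most 5% (4.94% if the outcomes are independent and neither truly differs), and it settles a mixed result: an outcome that passes its Holm step is claimed and the other is not. Naming the total score also brings 2.7.1 into line with 2.7.2.

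The cost is a few lines of text and some power. The first Holm step is at 2.5%, so the difference detectable there with 80% power at 40 complete cases per arm rises from about 0.63 to 0.70 SD of change. Dropout raises both figures.

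Ranking the two outcomes, or requiring both at 5%, would also control the error if the sponsor prefers. Whichever rule is chosen should be fixed before outcome data are compared between modalities.

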**Hypothesis** **3a2.**
*Basic psychological need satisfaction and autonomous motivation will mediate the relationship between the coach’s controlling interpersonal style and burnout in both the face-to-face and semi face-to-face modalities, at baseline and post-intervention.*

Specific Objective 3b. To evaluate the mediating effect of autonomous motivation between basic psychological need satisfaction and healthy lifestyle (mediating effect 3), as well as between basic psychological needs satisfaction and burnout (mediating effect 4), in both the face-to-face and semi face-to-face modalities, at baseline and post-intervention.

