**Hypothesis** **3b1.**
*Autonomous motivation will mediate the relationship between basic psychological need satisfaction and healthy lifestyle in both the face-to-face and semi face-to-face modalities, at baseline and post-intervention.*

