**Hypothesis** **3b2.**
*Autonomous motivation will mediate the relationship between basic psychological need satisfaction and burnout in both the face-to-face and semi face-to-face modalities, at baseline and post-intervention.*

Specific Objective 4. To evaluate the moderating effects of the type of participation (face-to-face and semi face-to-face) both at baseline and after the intervention as follows: (a) the relationship between the coach’s controlling interpersonal style and basic psychological need satisfaction (moderating effect 1); (b) the relationship between basic psychological need satisfaction and autonomous motivation (moderating effect 2); (c) the relationship between autonomous motivation and healthy lifestyle (moderating effect 3); and (d) the relationship between autonomous motivation and burnout (moderating effect 4).

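### The mediation clause for Objective 3b in section 2.6.1 exchanges predictor and mediator, so the indirect effect it plans does not test H3b1 or H3b2

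*Protocol article*

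**What the plan says.** Under Research Objectives and Hypotheses, Specific Objective 3b reads "To evaluate the mediating effect of autonomous motivation between basic psychological need satisfaction and healthy lifestyle" (mediating effect 3), and continues with the same structure for burnout (mediating effect 4). The hypotheses repeat that order. H3b1: "Autonomous motivation will mediate the relationship between basic psychological need satisfaction and healthy lifestyle". H3b2: "Autonomous motivation will mediate the relationship between basic psychological need satisfaction and burnout". Each is to hold in both modalities and at both occasions.

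The Mediation effects paragraph of section 2.6.1 opens with "The effects of basic psychological needs satisfaction and autonomous motivation as mediating variables" and lists in parentheses what will be evaluated. The first item is needs and motivation as mediators between coach style and the outcomes, which matches Objective 3a. The second item is "the effect of basic psychological needs satisfaction on the relationship between autonomous motivation, healthy lifestyle, and burnout".

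The decision criterion is given as "The significance of mediation inferred when the confidence interval of the indirect effect does not include zero", and the general rule is "All statistical analyses will consider a 95% confidence level (5% error". The paragraph ends by calling the mediation analyses exploratory.

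**The concern.** The second item has the same grammatical form as the first: the effect of a mediator on the relationship between a predictor and the outcomes. Read that way, need satisfaction is the mediator and motivation the predictor, which is Objective 3b with the two variables exchanged. The models share the same three variables but have different indirect effects.

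An analyst who follows 2.6.1 literally would produce a bootstrap interval for motivation → needs → outcome and could report it under H3b. One numbered objective and two named hypotheses would then have no matching analysis. That is two outcomes × two modalities × two occasions = 8 indirect effects. If the conflict stays open, either direction can be chosen after the data are seen and the protocol cited in support.

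**Working it through.** **Step 1: the texts side by side.**

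| Place | Predictor | Mediator | Outcomes |
|---|---|---|---|
| Objective 3b, H3b1, H3b2 | need satisfaction | autonomous motivation | lifestyle, burnout |
| 2.6.1, second mediation item | autonomous motivation | need satisfaction | lifestyle, burnout |
| 2.6.1, first mediation item (Objective 3a) | coach style | needs and motivation | lifestyle, burnout |

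The rest of the article supports the first row. The Introduction says that satisfied needs foster autonomous motivation. Hypothesis 1 runs coach style, needs, motivation, outcomes. Section 2.7.2 treats motivation as a mediating mechanism for both outcomes. No other sentence in 2.6.1 describes the 3b model.

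**Step 2: what each model estimates.** Let X = needs, M = motivation and Y = outcome, all standardised, with

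- M = aX + e
- Y = c'X + bM + e

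In the H3b order (X → M → Y) the indirect effect is a·b.

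In the order as written (M → X → Y), the first leg is the slope of X on M, which equals a when both are standardised. The second leg is the coefficient of X given M, which is c'. The indirect effect is a·c'.

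The path b, which H3b depends on, does not enter the quantity that 2.6.1 describes. For burnout the expected b is negative; signs change but the argument does not.

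**Step 3: size.** The plan gives no mediation effect size or power figure to reproduce. Section 2.2.4 gives 80 participants, 40 per modality, set on feasibility. The path values below are therefore assumptions, shown over a range. The simulation used 1,000 samples per row and 1,000 percentile-bootstrap resamples each, and counted 95% intervals that exclude zero. Each pair is H3b order / order as written.

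| a, b, c' | Indirect effect: a·b / a·c' | CI excludes 0, n = 40 | CI excludes 0, n = 80 |
|---|---|---|---|
| 0.5, 0.5, 0 | 0.25 / 0.00 | 75.3% / 5.2% | 98.4% / 5.6% |
| 0.3, 0.3, 0 | 0.09 / 0.00 | 21.2% / 2.6% | 58.1% / 4.5% |
| 0.5, 0.4, 0.1 | 0.20 / 0.05 | 57.6% / 9.1% | 92.1% / 16.9% |
| 0.5, 0.4, 0.2 | 0.20 / 0.10 | 62.8% / 21.5% | 92.6% / 45.6% |
| 0.5, 0.3, 0.3 | 0.15 / 0.15 | 42.0% / 39.5% | 72.9% / 76.2% |
| 0.5, 0.2, 0.4 | 0.10 / 0.20 | 22.5% / 61.9% | 45.7% / 94.0% |

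The n = 40 column is the relevant one, because the hypotheses are stated per modality. H3b is true in every row. Depending on c', the model as written gives nothing, the same value, or twice the value.

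**The case against.** The strongest reply is that this is a slip in half of one parenthetical clause. Every other relevant place gives the order needs, motivation, outcome, so a careful reader can recover the intended model. Mediation is explicitly exploratory, and neither the primary outcomes (change in lifestyle and in burnout) nor the comparison of modalities depends on it. All of that stands, and it lowers the severity. It does not remove the conflict: an exploratory label excuses imprecision, not estimating a different indirect effect.

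A second reply is that the pieces of H3b are covered elsewhere. Section 2.6.1 plans hierarchical regressions among all five variables, by modality and occasion, and the 3a model contains both needs and motivation. This stands in part, since the component associations are planned. But the product that H3b concerns is not stated. The 3a model starts from coach style, and the text does not say whether its two mediators act in series or in parallel.

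A third reply concerns the consequence, and it is right. A reader might infer that the model as written returns about zero whenever H3b1 and H3b2 are true, and so would reject a true hypothesis. The documents do not support that. The hypotheses say only that motivation mediates, not that it mediates completely, and no passage says the direct path from needs is near zero. The Introduction even describes well-being as promoted through need satisfaction without making motivation the only route. Nor would a null result for the exchanged model reject H3b, because that model does not test it.

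**Conclusion.** The contradiction is real and can be seen on the page. Section 2.6.1 names the wrong mediator for Objective 3b, and no indirect effect it states corresponds to mediating effects 3 and 4. The supported conclusion is that the analysis as written is uninformative about H3b in either direction. It can miss mediation by motivation, or report an indirect effect through needs that H3b does not claim.

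The 75% versus 5% contrast at n = 40 illustrates full mediation with assumed paths of 0.5 and should not be quoted as the general result. With weaker paths of 0.3, even the correct model has an interval excluding zero in only 21% of samples, so the correction restores the right question but does not guarantee power to answer it.

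The algebra in step 2 rests only on the linear standardised model. The percentages rest on assumed coefficients, normal data and complete samples of the stated size. Severity is moderate.

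**What to change.** In the Mediation effects paragraph of section 2.6.1, replace the second item with: *as well as the mediating effect of autonomous motivation on the relationships between basic psychological needs satisfaction and (i) healthy lifestyle and (ii) burnout*. Estimate the indirect effect as needs → motivation → outcome, in each modality and at each occasion, as Objective 3b requires.

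If the authors do want motivation → needs → outcome as well, it should be added as a separate, labelled exploratory model and not reported under H3b.

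The cost is one clause of wording, made before the analysis. It changes no data collection, sample size or staffing.
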